### Sampling

According to the Burden of Obstructive Lung Disease (BOLD) protocol, a minimal sample size of 600 is recommended to achieve an acceptable level of precision for estimating COPD prevalence [29]. Our goal is for a sample size of 900 including 500 smokers, 200 ex-smokers, and 200 never-smokers. We have used the National Health and Nutrition Examination Surveys data to assume COPD prevalence in these 3 groups [30]. The sample size of 500 allows for achieving the precision of 3.5% with the expected prevalence of obstructive impairment of 20%. The sample size of 200 and the expected prevalence of pulmonary obstruction of 10% and 2% among ex-smokers and never-smokers, respectively, provides sample estimates with 4.2% and 1.9% precision, respectively [31].

The 3 study groups are planned to have the same gender and age distribution by implementing age-gender quota to eliminate age and gender potential confounding effect to the associations between smoking status and outcomes.

It was shown that the sample characteristics depend on recruitment method used [32]. To recruit study participants, active and passive approaches are used. Participants are recruited by using personal networks of investigators and persons who are already participating in the study (snowball), placing an advertisement of the study in social media (Facebook) targeting those individuals who are potentially eligible to participate (live in Almaty, specific age group), and meeting with the owners and managerial staff of several large companies located in Almaty to explain the benefits of participation in the study. Employees of these companies who are potentially eligible to participate in the study are contacted by phone calls.

### Study Procedures

The study flow is shown in  Figure 1. Participants are expected to attend 2 to 3 visits for the study, for a total of about 3 hours. Completing study procedures for each participant, including sharing the study results with the participant, is expected to take up to 2 weeks.

**Figure 1 figure1:**
[figure not shown]
Patient recruitment, enrollment, and data collection and sharing.

#### Spirometry

Spirometry is performed by trained investigators, with 3 technically satisfactory maneuvers performed by each study participant. The largest value of FEV_1_ and the respective value FVC are selected to calculate ratio of FEV_1_ to FVC. The CardioTouch 3000-S (BiTech Medical Corp), a 12-lead resting electrocardiogram (ECG) machine with a spirometer with a measuring accuracy that complies with American Thoracic Society requirements [33], is used to perform lung function tests. Calibration of the spirometer was performed every day before using it. A 3-L syringe was pumped through to check that accuracy did not exceed a tolerance of 3% [33].

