## Introduction

Chronic obstructive pulmonary disease (COPD) is the fourth leading cause of death worldwide [1]. The number of affected individuals and deaths from COPD are expected to increase as the population ages [2]. In Russia, the largest neighboring country of Kazakhstan, the prevalence of symptomatic COPD in the adult population was estimated to be 15.3% [3]. An estimated 1.4 million individuals in Kazakhstan may be affected by COPD. This estimate is based on studies that have been conducted in other countries in the World Health Organization European Region [4] but not in Kazakhstan, because a study on the prevalence of COPD has not been conducted in the country yet. COPD is significantly underdiagnosed in Kazakhstan. In 2013, the rate of reported COPD cases was 315.9 per 100,000 or around 53,000 registered cases of COPD [5]. A better understanding of the epidemiology and social and other determinants of the disease is needed in order to recognize the true magnitude of the problem and develop effective treatments and prevention strategies.

Various criteria for COPD have been used in population-based studies. The most common criterion is airflow obstruction detected by spirometry testing, defined as a postbronchodilator ratio of forced expiratory volume in 1 second (FEV_1_) to forced vital capacity (FVC) less than 0.7 or 70% [6]. This criterion is simple to implement and widely used in epidemiological surveys. However, COPD prevalence based on this could be slightly biased—overestimated in old subjects and underestimated in younger ones [7]. For this reason, the fifth percentile of the FEV_1_/FVC ratio or the lower limit of normal distribution of the FEV_1_/FVC ratio defined for specific age-gender group is also recommended for use in epidemiological studies [8].

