## Methods

### Study Design

This is an observational study with a cross-sectional design to assess the prevalence of COPD in Almaty, Kazakhstan, among individuals aged 40 to 59 years based on results of spirometry, the presence of structural changes in the lungs, and symptoms of COPD.

The study population is 3 groups of male and female residents of Almaty, the largest city in Kazakhstan, with a population of 1.7 million people, 9% of whom are aged 40 to 59 years. Members of the first group include current smokers with more than a 10 pack-year history of smoking (smokers). The second group comprises individuals who quit smoking from 1 to 5 years ago and have more than a 10 pack-year history of smoking (ex-smokers). The third group comprises persons who have never smoked regularly (ie, smoked less than 100 cigarettes in their lifetime) (never-smokers).

We recruited individuals who are 40 years of age or older because most people are at least 40 years old when the symptoms of COPD first appear [23]. The same age limit is selected for many COPD prevalence studies [24-26]. The upper age was set at 59 years to avoid survival bias [27] possibly leading to underestimating the effects of risk factors on COPD. We have taken into account that the life expectancy at birth among males was only 66 years in Kazakhstan in 2015 [28].

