#### Computed Tomography

Study subjects undergo 64-channel CT scans of the chest (Philips Brilliance CT 64). Subjects with restrictive (FEV_1_/FVC from 70% to 80%) and obstructive (FEV_1_/FVC less than 70%) lung diseases or signs and symptoms of COPD found during the physical examination and survey undergo inspiratory-expiratory CT scans obtained at the following settings: detector collimation 0.6-0.75 mm, 0.625-0.9 mm reconstructed slice thickness, 0.45-0.625 mm slice interval, 120 kV, 200 (inspiratory) and 50 (expiratory) mAs. Other subjects have only inspiratory CT scans: 0.8 mm reconstructed slice thickness, 0.4 mm slice interval, smooth reconstruction algorithm iDose 7, matrix size 512×512, range = –500 to 1500, 120 kV, 40 mAs [34].

CT scans are evaluated by 3 independent qualified observers to produce semiquantified measures that characterize the extent of emphysema, severity of bronchial dilatation, traction bronchiectasis, bronchial wall thickening, and small airway disease. We use the Bhala scoring system [35] modified by Tulek at al [36]. The kappa test will be used to evaluate interrater reliability of visual CT scan analysis. The median score by 3 observers will be recorded for each participant.

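### FEV1/FVC takes the best of three manoeuvres for the numerator but not for the denominator, so the share below 0.70 can only equal or fall short of the largest-FVC figure

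*Protocol article*

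**What the plan says.** The Spirometry section of the protocol article plans the test "with 3 technically satisfactory maneuvers performed by each study participant". It then fixes how the ratio is derived: "The largest value of FEV_1_ and the respective value FVC are selected to calculate ratio". The article does not mention the largest FVC across manoeuvres, and it gives no reason for pairing the two values within one manoeuvre.

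The ratio matters in three places:

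- The Introduction gives a post-bronchodilator ratio below 0.70 as the most common criterion for airflow obstruction.
- The Study Design section assesses COPD prevalence "based on results of spirometry, the presence of structural changes in the lungs, and symptoms of COPD".
- The Sampling section rests the sample size on obstruction. For smokers: "The sample size of 500 allows for achieving the precision of 3.5% with the expected prevalence of obstructive impairment of 20" (per cent). Ex-smokers and never-smokers (200 each) are planned at 10% and 2%, with precision of 4.2% and 1.9%.

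**The concern.** The rule treats the two halves of the ratio differently. FEV1 is the maximum of three values. FVC is whatever came with it, and it may be smaller than an FVC the same person achieved on another satisfactory manoeuvre. When it is smaller, the denominator shrinks and the ratio rises. No arrangement of the three manoeuvres makes the ratio fall.

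Some participants who would be below 0.70 with their largest FVC are then counted as not obstructed, and nobody moves the other way. The estimated prevalence of obstruction is shifted downwards relative to the largest-FVC rule. The confidence interval does not show the shift, and recruiting more people does not shrink it.

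**Working it through.** **1. The plan's own precision.** Half-width = 1.96 × √(p(1−p)/n).

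| Group | n | p | Half-width | Stated |
|---|---|---|---|---|
| Smokers | 500 | 0.20 | 3.51% | 3.5% |
| Ex-smokers | 200 | 0.10 | 4.16% | 4.2% |
| Never-smokers | 200 | 0.02 | 1.94% | 1.9% |

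The stated figures reproduce. They are the yardstick below.

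**2. Direction.** Let F be the largest FEV1, V_s the FVC of that manoeuvre and V_m the largest of the three FVCs. Since V_s ≤ V_m, F/V_s ≥ F/V_m, with equality when the same manoeuvre gives both maxima. A participant changes class only if F/V_m < 0.70 ≤ F/V_s. Example: F = 2.80 L, V_s = 3.95 L, V_m = 4.05 L. The plan's rule gives 2.80/3.95 = 0.709 (not obstructed). The largest-FVC rule gives 2.80/4.05 = 0.691 (obstructed).

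**3. Size with one-sided errors (assumed).** The article gives no between-manoeuvre variability, so every error input here is an assumption. True ratios are normal with SD 0.07, centred so that 20% lie below 0.70. Each person has three manoeuvres, and errors only lower the values (half-normal). With no correlation between FEV1 and FVC errors within a manoeuvre:

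| FEV1 scale | FVC scale | Same manoeuvre | Largest FVC | Shortfall |
|---|---|---|---|---|
| 1.5% | 2% | 17.3% | 19.6% | 2.3 |
| 2% | 3% | 15.9% | 19.2% | 3.3 |
| 2% | 4% | 14.3% | 18.3% | 4.0 |
| 3% | 3% | 16.8% | 20.2% | 3.4 |

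For the same four settings the shortfall is 1.5-2.6 points at correlation 0.7 and 0.7-1.3 points at 0.9. These correlations belong to the normal deviates before they are folded to one side. The folded errors correlate (2/π)(√(1−ρ²) + ρ·arcsin ρ − 1)/(1 − 2/π), which is 0.45 at ρ = 0.7 and 0.78 at ρ = 0.9. In 500 smokers, 0.7-2.6 points is 500 × 0.007 = 3.5 to 500 × 0.026 = 13 people.

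**4. Size with symmetric errors (assumed).** Here prevalence under the largest-FVC rule is set to 20%, and FEV1 and FVC have the same coefficient of variation (CV). Entries are the smokers' prevalence under the same-manoeuvre rule.

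| CV | correlation 0.3 | 0.7 | 0.9 |
|---|---|---|---|
| 1% | 18.5% | 19.3% | 19.8% |
| 2% | 17.0% | 18.7% | 19.5% |
| 3% | 15.9% | 18.1% | 19.3% |
| 4% | 15.0% | 17.6% | 19.1% |

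The shortfall runs from 0.2 to 5.0 points. It exceeds 3.5 only at correlation 0.3 with CV 3% or 4% (4.1 and 5.0). Over the same grid it is 0.1-2.9 points in ex-smokers (precision 4.2) and 0.05-0.7 in never-smokers (precision 1.9). The two rules agree exactly in 45%, 64% and 79% of participants at correlations 0.3, 0.7 and 0.9. In no simulated participant was the same-manoeuvre ratio the lower one.

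**5. Which rule is nearer the truth.** With the one-sided errors of step 3 at zero correlation, the largest-FVC figure was closer to 20% in all four settings. With symmetric errors this is not general. At FEV1 2%, FVC 3% and correlation 0.7, with a true 20%, the plan's rule gives 20.7% and the largest-FVC rule 22.8%, so the plan's rule is closer. With equal 2% or 3% errors the largest-FVC rule is closer.

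**The case against.** The best defence is that this is a choice of definition with an unknown effect. Being below the largest-FVC figure is a bias only if that figure is taken as the truth, and step 5 shows that it need not be. The premise that FVC errors run mainly one way is not in the article. The requirement for technically satisfactory manoeuvres, performed by trained investigators, is meant to limit such errors. FEV1 is also part of the same expiration as FVC, so zero correlation is the least favourable non-negative assumption for the plan. All of this stands, and it limits the claim to a one-directional difference between two rules. It does not remove the difference or explain why only the numerator is maximised.

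A reader might infer more than the article supports:

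- **That the shift is as large as the sampling error.** It reaches 3.5 points only with large errors that are weakly correlated or uncorrelated.
- **That it decides who gets the fuller CT scan at the 70% cut.** The Computed Tomography section gives the inspiratory-expiratory scan to people with "obstructive (FEV_1_/FVC less than 70%) lung diseases" and equally to those with ratios of 70-80%, so crossing 70% changes no one's scan.
- **That it affects every prevalence in the study.** COPD is also assessed by CT and symptoms, and the comorbidity, ECG and physical-examination prevalences do not use this ratio as their numerator.
- **That the plan uses only the fixed 0.70 cut.** The Introduction says of that cut that "COPD prevalence based on this could be slightly biased" and notes that the lower limit of normal is also recommended. The Statistical Analysis section neither adopts nor excludes it. Silence in a condensed article is not evidence of exclusive use.

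The word used for the FVC is also loose. If the largest FVC was in fact used, only the wording needs correcting.

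**Conclusion.** The point holds in a limited form. As written, the rule gives a ratio equal to or above largest FEV1/largest FVC in every participant, and therefore an equal or lower prevalence of obstruction. This is certain and needs no outside source.

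The size rests on assumed variability. At a true 20% with one-sided errors, it is about 0.7-2.6 points when FEV1 and FVC errors are correlated (0.7-0.9 before folding), and up to about 4 points when they are not. That is usually inside the 3.5-point precision planned for smokers. It still matters because it pushes one way, on the measure that the sample size was built for, and the interval does not reflect it. Whether the plan's figure undercounts the true prevalence cannot be settled from the article: it does under the one-sided errors assumed here, but not in every symmetric-error setting.

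**What to change.** State explicitly which FVC enters the ratio. Derive the post-bronchodilator FEV1/FVC as the largest FEV1 divided by the largest FVC over the three satisfactory manoeuvres, even when they come from different ones. Report prevalence with the same-manoeuvre ratio as a sensitivity analysis, so that the dependence on the rule is visible in the study's own data.

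The Results section says that recruitment and procedures are complete and that analysis is under way. If all three manoeuvres were stored, which the article does not say, the cost is one re-derived variable and one extra column in the prevalence table. If only the selected pair was stored, the rule and its one-way direction should be stated as a limitation. The downside is that a few more participants are classed as obstructed, and under some symmetric-error patterns that would be an overcount. Reporting both versions covers this.

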#### Computed Tomography

Study subjects undergo 64-channel CT scans of the chest (Philips Brilliance CT 64). Subjects with restrictive (FEV_1_/FVC from 70% to 80%) and obstructive (FEV_1_/FVC less than 70%) lung diseases or signs and symptoms of COPD found during the physical examination and survey undergo inspiratory-expiratory CT scans obtained at the following settings: detector collimation 0.6-0.75 mm, 0.625-0.9 mm reconstructed slice thickness, 0.45-0.625 mm slice interval, 120 kV, 200 (inspiratory) and 50 (expiratory) mAs. Other subjects have only inspiratory CT scans: 0.8 mm reconstructed slice thickness, 0.4 mm slice interval, smooth reconstruction algorithm iDose 7, matrix size 512×512, range = –500 to 1500, 120 kV, 40 mAs [34].

CT scans are evaluated by 3 independent qualified observers to produce semiquantified measures that characterize the extent of emphysema, severity of bronchial dilatation, traction bronchiectasis, bronchial wall thickening, and small airway disease. We use the Bhala scoring system [35] modified by Tulek at al [36]. The kappa test will be used to evaluate interrater reliability of visual CT scan analysis. The median score by 3 observers will be recorded for each participant.

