**Objective:**

The purpose of this study is to assess the prevalence of COPD among individuals aged 40 to 59 years based on results of spirometry before and after bronchodilator, presence of structural changes in the lungs (emphysema, inflammatory changes, and thickening of the walls of the large and small airways) detected by computer tomography, and the symptoms of COPD. The study has 3 study groups: smokers of conventional cigarettes, those who had quit smoking 1 to 5 years ago, and those who haven’t smoked cigarettes.

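### CT acquisition depends on spirometry and symptoms, so score items that need an expiratory scan are biased towards an association with COPD and, probably, with smoking

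*Protocol article*

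**What the plan says.** The Computed Tomography section sets two acquisitions. The first has this trigger: "Subjects with restrictive (FEV_1_/FVC from 70% to 80%) and obstructive (FEV_1_/FVC less than 70%) lung diseases or signs and symptoms of COPD found" at the examination or survey. Those participants "undergo inspiratory-expiratory CT scans obtained at the following settings", which include "0.45-0.625 mm slice interval, 120 kV, 200 (inspiratory) and 50 (expiratory) mAs". All others follow the second: "Other subjects have only inspiratory CT scans: 0.8 mm reconstructed slice thickness, 0.4 mm slice interval", with "smooth reconstruction algorithm iDose 7, matrix size 512×512, range = –500 to 1500, 120 kV, 40 mAs".

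Reading is common to both: "CT scans are evaluated by 3 independent qualified observers to produce semiquantified measures that characterize the extent of emphysema", together with bronchial dilatation, traction bronchiectasis, wall thickening and small airway disease. The median of the three observers' scores is recorded for every participant.

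CT also feeds the main aim. The Objective bases COPD prevalence on spirometry, symptoms and "presence of structural changes in the lungs (emphysema, inflammatory changes, and thickening of the walls of the large and small airways"; the Introduction and Study Design sections say much the same. The Sampling section, by contrast, sizes the study on airflow obstruction alone, for example "precision of 3.5% with the expected prevalence of obstructive impairment of 20"% in 500 smokers.

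**The concern.** One score pools two measurement procedures, and the procedure a participant gets is decided by the criteria that define COPD in this study. A sign visible only on expiration cannot be recorded in someone without an expiratory series. Every obstructed participant has that series, but only some of the non-obstructed do, so part of any association between such a sign and COPD is produced by the design. Obstruction is expected to be far commoner in smokers, so part of a smoking contrast may be produced in the same way.

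The affected results are the CT-COPD associations, the comparison of small-airway findings across smoking groups, and any COPD count that uses those findings. Covariate adjustment, on which the Discussion relies, does not help: asymptomatic participants with a ratio above 80% have no chance of an expiratory scan, so no weight or model recovers what it would have shown. The limitations listed in the Discussion do not mention this.

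**Working it through.** **Inputs from the article.** Expected obstruction: 20% of 500 smokers, 10% of 200 ex-smokers, 2% of 200 never-smokers (Sampling). Trigger: ratio of 80% or less, or signs or symptoms (Computed Tomography). The share of participants meeting the full trigger is not given for any group.

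**Stated figures first.** Half-width = 1.96 × √(p(1−p)/n):
- smokers: 1.96 × √(0.20 × 0.80/500) = 3.51% (stated 3.5%)
- ex-smokers: 1.96 × √(0.10 × 0.90/200) = 4.16% (stated 4.2%)
- never-smokers: 1.96 × √(0.02 × 0.98/200) = 1.94% (stated 1.9%)

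All three reproduce, so 20%, 10% and 2% are sound inputs.

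**CT-COPD association.** Let q be the share of non-obstructed participants who are triggered (assumed). Let an expiratory-only sign have the same true prevalence π in obstructed and non-obstructed participants, and be unrelated to triggering among the latter. Recorded prevalence is π in the obstructed and qπ in the non-obstructed, so the recorded ratio is 1/q when the true ratio is 1:
- q = 30%: 3.3
- q = 50%: 2.0
- q = 70%: 1.4

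If the sign is partly visible on inspiration, the ratio is s₁/(q·s₁ + (1−q)·s₀), where s₁ and s₀ are the detection rates with and without the expiratory series. At q = 50% and s₁ = 0.9 (assumed):
- s₀ = 0.3: 0.9/(0.45 + 0.15) = 1.5
- s₀ = 0.6: 0.9/(0.45 + 0.30) = 1.2

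The bias shrinks but stays.

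**Smoking contrast.** Share with an expiratory scan = p + (1−p)q, where p is expected obstruction.

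| Assumed q, smokers / never-smokers | Smokers | Never-smokers | Ratio |
|---|---|---|---|
| 0 / 0 (obstruction trigger only) | 20% | 2% | 10 |
| 10% / 10% | 28% | 11.8% | 2.4 |
| 30% / 30% | 44% | 31.4% | 1.4 |
| 70% / 70% | 76% | 70.6% | 1.08 |
| 30% / 10% | 44% | 11.8% | 3.7 |
| 50% / 30% | 60% | 31.4% | 1.9 |
| 70% / 50% | 76% | 51% | 1.5 |

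The first row ignores the 70–80% band and the symptom trigger, so it is not a realistic case. The others run from about 1.1 to 3.7.

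A second route assumes a normal FEV1/FVC with a common SD and a mean that gives the stated obstruction rate, ignoring symptoms. With SD 0.07, the mean is 0.70 − 0.07·z(p):
- smokers: 0.759, so P(ratio ≤ 0.80) = 72.1%
- never-smokers: 0.844, so P(ratio ≤ 0.80) = 26.6%

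The ratio is 72.1/26.6 = 2.7. An SD of 0.06 gives 80% v 35%, and 0.08 gives 66% v 21%. For a sign seen only on expiration and truly present in 20% of both groups (assumed), SD 0.07 gives recorded prevalences of 0.20 × 72.1% = 14.4% and 0.20 × 26.6% = 5.3%.

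**Acquisition compared on the inspiratory series.** Tube current-time differs (200 v 40 mAs), as does slice interval (0.45–0.625 v 0.4 mm). Both use 120 kV, and 0.8 mm thickness lies within the two-phase range of 0.625–0.9 mm. A smooth reconstruction is stated for the single-phase scans; none is stated for the two-phase scans, so a difference there is not documented.

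**The case against.** Every participant has an inspiratory CT and a score. The structural changes named in the Objective are emphysema, inflammatory change and wall thickening; gas trapping appears only as background in the Introduction. The article does not show whether the scoring system grades small airway disease from expiratory images. This stands as a limit: the bias applies to items that depend on expiration, and the article does not say which those are. It does not remove the point, because small airway disease is scored for everyone from unequal material.

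A reader might infer that small-airway findings are sought far more often in smokers than in never-smokers. The documents do not support that strength. The trigger includes a wide ratio band and any sign or symptom, with no rates given. The 72% v 27% rests on an assumed distribution and a pure mean shift; with equal trigger rates among the non-obstructed, the contrast can be close to 1. Very low ratios need non-obstructed smokers and never-smokers to trigger equally often, which is possible but not the natural expectation.

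A reader might also infer that the observers can see who is abnormal. An expiratory series, if shown, reveals only that the trigger was met. That includes people in the 70–80% band without obstruction or symptoms, and it does not identify the smoking group. Masking and reading instructions are commonly left to the full protocol, so the article's silence on them is not a fault.

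**Conclusion.** The point holds for score items that depend on expiration. Their association with COPD is biased upward for any q below 100%: by 1/q (1.4 to 3.3 for assumed q of 70% to 30%) if the sign is seen only on expiration, and by less if it is partly visible on inspiration or commoner among triggered than untriggered non-obstructed participants. The smoking-group comparison is probably biased towards smokers, unless never-smokers meet the other triggers sufficiently more often. Its size is not determined by the documents: about 1.1 to 3.7 over the assumed trigger rates, 2.7 under the normal model with SD 0.07. No direction can be given for the effect of the mAs difference on inspiratory items.

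Severity is moderate. It would go too far to say that the study's prevalence estimates are undermined as a whole, since spirometric obstruction, the quantity the sample was sized for, is untouched. Nor does the point require COPD to be redefined as obstruction alone; that is a separate choice of case definition and would change the stated aim.

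**What to change.** 1. Base between-group and CT-COPD comparisons on items scored from the inspiratory series. Where reading is not yet done, read that series without the expiratory series or spirometry. Where it is done, restrict the comparison to items readable on inspiration, and list them.
2. Report expiratory-dependent small-airway findings only within the two-phase subset, with no prevalence by smoking group.
3. Because the inspiratory scans still differ in mAs, add a sensitivity analysis by acquisition protocol and state the difference as a limitation. Tabulate how many in each smoking group had each protocol, which replaces the assumed trigger rates above with observed ones.
4. Report spirometric obstruction separately from any COPD count that uses CT.

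Recruitment and procedures are complete and analysis is under way, so the cost is wording in the analysis and reading instructions, plus one table and one sensitivity analysis. No rescanning is needed and no scan setting is proposed. The price is that expiratory findings cannot be compared across smoking groups.
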